#### Health outcomes measures

We have selected a range of health outcomes to explore, informed by epidemiological evidence. Our primary health outcome will be changes in respiratory health outcomes assessed by Accident and Emergency (A&E) and GP attendances overall and stratified by age group: children (0 – 17 years), adults (18 – 64 years), and older adults (65+). Our secondary analyses will examine cardiovascular outcomes in adults (stratified by age groups defined above), and birth outcomes (pre-term birth and low birth weight), see Table 3.

**Table 3 Tab3:** Description of health outcomes

Health Outcomes	CTV3 and ICD-10 codes	Length of follow up	Life-course stage
**PRIMARY**: Respiratory health: A&E / GP attendances, assessed weekly	CTV3 codes: XaKyZ, Xa9Bt, X00n8, X00n9, H27.., H270., XM0rz, XaIBK, H2700, X100E, Xa0lY, XE0YG, XaDsa, X100H, Xa7nL, H200., X100J, XM0rv, Xa7nU, Xa7nT, Xa7nP, XE0YH, XaJEl, Xa7nL, Xa7nN, Xa7nM, X100M, XE0Xt, XE0Xs, XE0Xr, X100B, X1007, XSDOK, H061., X100C, H0615, XaYYt, XaDtP, H30z., H31.., H310., XaDtg, Xa87h, H32.., H3..., H3z.., XaEIV, XaEIY, XaEIW, XaN4a, H33.., X101x, XE0YX, 663 V1, H332., 663 V2, 663e., 663P., 663 N2, XaXZx, XE0YW, 663 N0, 663 N., 663 N1 ICD-10 codes: Respiratory infection (J05.0, J10-J16, J18, J20, J21); bronchitis (J40 – J42); asthma (J45); COPD (J43-J34)	1 year (interim) and 3 years post implementation	Children Adults Older adults
**SECONDARY**: Cardiovascular health: A&E / GP attendances, assessed weekly/monthly	CTV3 codes: XE2uV, G3z.., G33.., G33z., Ua1eH, X200E, XE0Uh, G35.., G30y., G305., G301z, G304., Xa0YL, G308., XE0WC, G3110, G312., G70.., XM0rN, XE2uV, XE2aA, G341., XM1Qk, G3410, G3412, G343., X200D, XE0WG, G34.., G34z., X202Z, G561z, XE2QF, X202a, G560., G5610, X202d, G5620, XaRCL, Xa0lU, G565., G564., X77Ab, G5654, X202Y, XE0We, G56zz, XE0V5, X202n, XaC2L, X2025, G570., XE0V4, G572z, G5730, G573., G5740, G574., G58.., XE0V9, X202l, XE2QG, XE0V8, Xa1uW, G60z., XE0VF, G61z., XA0BG, Xa0kZ, XE0VJ, X00D1, XaEGq ICD-10 codes: Angina/MI (I20-I22, I24, I25); dysrhythmia/conduction disturbance (I44-I49); heart failure (I50); stroke (haemorrhage or infarction; I60-I64))	1 year (interim) and 3 years	Adults Older adults
**SECONDARY**: Birth outcomes, assessed monthly	ICD-10 codes: Pre-term birth (< 37 weeks gestation: O60.1, 060.3, P07.2, P07.3) and low birth weight (< 2.5 kg: P07.0, P07.1)	3 years	Children

We will explore health inequalities in detail for respiratory health amongst children using the BiB data set.

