### Aims and objectives

We aim to assess the impact of the B-CAP on attitudinal, behavioural, air pollution and health outcomes, and establish its cost-effectiveness, using a multi-outcome, multi-sector approach. We also aim to explore the factors influencing any impact (or lack thereof) and explore unintended or unanticipated outcomes. The impact of the B-CAP on health inequalities amongst different socio-economic and ethnic groups will be assessed across all outcomes. Our findings will enable the modelling of potential health impacts of a CAZ approach within other cities in the UK and internationally.

Our research questions are as follows:What are the key barriers and enablers to implementation of the B-CAP (including acceptability), and are there unintended consequences of the B-CAP for different stakeholder groups (e.g., increased health and economic inequalities)?Does the B-CAP affect travel choice behaviour and attitudes amongst people who live or work in Bradford at 12 months post implementation?Does the B-CAP reduce exposure to pollution amongst primary school age children up to 12 months post implementation?What is the impact of the B-CAP 3 years post-implementation on:respiratory health (primary outcome, as assessed by weekly counts of respiratory disease related emergency hospital or General Practice [GP] attendance) of children (aged < 18), adults (aged 18-64) and older adults (aged 65+)cardiovascular health (as assessed by weekly counts of cardiovascular disease related emergency hospital/GP attendance) of adults and older adults;birth outcomes such as low birth weight and preterm birth (assessed by monthly counts)How does the B-CAP impact on health inequalities up to 3 years post implementation?What is the value for money of the B-CAP 3 years post-implementation and longer term?

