### Study population

For our primary analysis (WP3A), we plan to take a whole city/district, life-course approach. Using our connected data set of linked routine health data from over 500,000 Bradford residents we will explore outcomes across the population, before stratifying into three groups (children: at birth and 0-17 years; adults: 18-64 years; and older adults (65 years+). Key health outcomes will be extracted from this dataset to provide a comprehensive analysis of any effect of the B-CAP on population health outcomes.

In addition to this whole city evaluation we will harness the rich data from the BiB cohort of 12,500 Bradford families and 13,500 children for whom we have detailed longitudinal health and wellbeing assessments (including routine data) and rich socio-economic and ethnicity information. This cohort will allow us to provide more detailed insights into the effect of the B-CAP on health inequalities, and to interrogate our proposed logic model. BiB is a representative research-active cohort of families with children born in the city between 2007 and 2011 (~ 60% of the eligible population at time of recruitment). Approximately 85% of the cohort is still resident within Bradford. Fifty percent of mothers in the cohort are of South Asian origin, which was broadly representative of births in the city during the period of recruitment [41]. All of the parents in the cohort are of working age. Routine linked health data is available for 99% of parents and children (which also allows geocoded address information to be captured monthly from primary care records), and education data is available for 85% of children. In addition to these large datasets, other elements of the evaluation will focus on bespoke data collection with key groups including decision makers and stakeholders who have been involved in implementation of the B-CAP plans; and with members of the public, schools and families living in and around the CAZ boundaries.

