We have reviewed methods to inform power calculations; there are no accepted guidelines for calculating power in ITS designs [65, 66]. Power is dependent on a variety of factors including the length of the time series (with some suggesting 100 observation points required for correct model identification), [67] the balance of time points before and after the intervention, the expected effect size, the extent of autocorrelation between the data points, and sample size per time point. Power increases in a balanced ITS design; in WP3 our proposed study would increase the power by ensuring roughly equal number of data points for the 3 years pre- and 3 years post-implementation. We illustrate the potential power of our analyses for our primary outcome, respiratory health (measured as emergency/GP admissions): in pilot analysis of a subsample of our connected data set (*N* = 316,585, assessed between Jan 2016-Dec 2018) we observed an average of 380 respiratory attendances per week suggesting adequate counts per observation period. Using weekly counts will give us a total of 312 observation points over a 6 year period. Guidance from simulations of Winquist et al. [66] suggests we will have > 90% power to detect a 2% reduction in admissions. For our secondary outcomes (cardiovascular/birth) we will assess counts either weekly or monthly depending on prevalence. Using monthly events a balanced design would give us 72 evenly distributed observations points. We will explore increasing the baseline intervention trend period by 28 months (e.g. 5 years pre-implementation) to ensure we can maintain 100 observation points (which is acceptable if there are no other major changes in pre-intervention trends in that time period) [65].

In WP3B we will focus only on respiratory attendances within the BiB cohort using similar methods. For these analyses we will have fewer events per observation period and so will perform analyses using either weekly or monthly counts.

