We will examine time-series line plots of the health outcomes to aid identification of underlying trends and seasonal patterns of the data. As the outcomes are counts, the Poisson link function will be used in the regression model. Models will be adjusted for age, sex, ethnicity, and measures of SES such as IMD. The coefficients from this regression can be used to estimate the intervention effect (the absolute difference between the predicted outcome based on the B-CAP and its counterfactual value, i.e. the expected values for level and trend if the intervention had not occurred. We will account for the disruption caused as a result of the COVID-19 pandemic, and the subsequent changes in behaviour including alterations to travel behaviour and A&E and GP attendances, through the selection of change points used in the segmented regressions. In England, the first lockdown was implemented on the 23rd of March 2020 and the third ended on the 31st July 2021. We will therefore consider four segments for our analysis: (1) the period prior to the first national lockdown from when clinical data of sufficient quality was available (October 2017 – March 2020); (2) the period spanning the lockdowns (March 2020 – August 2021); (3) the period encompassing the preparation phase for the CAZ (August 2021 - CAZ switch on, this includes other activities within the B-CAP including provision of grants for vehicle upgrades); (4) the period post ‘switch on’ of the charging CAZ). We will conduct an interim analysis at 12 months post-implementation and re-examine analyses 3 years post-implementation.

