### Follow-up

We have included a range of outcome measures that are likely to reflect shorter (A&E/GP attendances related to respiratory and cardiovascular disease), and longer term effects (birth outcomes). The B-CAP is mandated to improve air quality to compliant levels in ‘*as quick a time as possible’*. Based on modelling, the likely impact of measures included within the CAZ, compliance is due to be achieved 1 year post implementation, with gradual ongoing improvements over time. However, research has shown there is no ‘safe’ level of pollution for health, thus any improvements in air quality are likely to have an impact on health, regardless of whether they are above, or below legal limits [58]. Evidence has shown an immediate temporal relationship between increases in pollution and hospital attendances [60] thus we would expect to see an immediate reduction in emergency and GP attendances related to respiratory (adults and children) and cardiovascular (adults only) events provided the B-CAP is successfully implemented. Our other outcomes (birth outcomes) are likely to show an effect in the longer term. We have chosen 3 years as our primary follow-up period to measure effectiveness (with an interim reporting period at 1 year) period in order to provide timely evidence for decision makers, including other local authorities on the health impacts of CAZ approaches to improving air quality. As our primary analysis relies on routine data we have the unique opportunity to revisit our study populations beyond the lifetime of the planned research to provide even longer term follow-ups of the health outcomes outlined in Table 3. We have chosen a 1 year follow up for our process and evaluation outcomes to ensure timely capture of challenges related to implementation, and identification of the proximal effects by which the intervention might have an impact on outcomes.

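### The protocol does not fix which of four 3-year respiratory analyses (all ages, children, adults, older adults) is the primary one, and its definitions of the primary outcome disagree

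*Protocol article*

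**What the plan says.** The protocol article describes the population of the primary respiratory outcome in five places.

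- **Aims and objectives.** The research question marks respiratory health as the primary outcome and attaches it to "children (aged < 18), adults (aged 18-64) and older adults (aged 65" and over). No all-age analysis is named.
- **Health outcomes measures, text.** The primary outcome is "changes in respiratory health outcomes assessed by Accident and Emergency (A&E) and GP attendances overall and stratified by age group", followed by the same three age bands.
- **Health outcomes measures, Table 3.** The primary row lists children, adults and older adults as life-course stages. It has no all-age entry.
- **Power calculations.** Power for the primary outcome is illustrated on one undivided series: "we observed an average of 380 respiratory attendances per week suggesting adequate counts per observation period". No age split is given.
- **Study population.** For the primary analysis, "we will explore outcomes across the population, before stratifying into three groups".

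On timing the article is clear. Follow-up states: "We have chosen 3 years as our primary follow-up period to measure effectiveness (with an interim reporting period at 1 year". Table 3 and Analysis methods also call the 1-year analysis interim.

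**The concern.** A primary outcome should lead to one analysis whose result answers the main question, or to a stated rule for combining several. Here one section gives three analyses, another gives four, and the power statement supports one. The one that is powered, the all-age count, is missing from both the research question and the table.

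This matters because the age groups may well differ. The Power calculations section itself cites evidence of stronger effects in children and the elderly. Suppose attendances fall in children and the all-age count does not change. Under Aims and objectives a primary question has been answered favourably. Under a reading that puts the all-age count first, the primary result is null. Both reports could cite the protocol. The choice would then be made with the results in view, and with four candidates the chance of finding at least one apparent effect exceeds that of a single test.

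**Working it through.** **1. Definitions side by side (3-year time point)**

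| Place | All ages | Children | Adults | Older adults |
|---|---|---|---|---|
| Aims and objectives | no | yes | yes | yes |
| Health outcomes measures, text | yes | yes | yes | yes |
| Table 3, primary row | no | yes | yes | yes |
| Power calculations | yes (380 a week) | no | no | no |

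No two of the three kinds of statement agree, and none ranks the four analyses.

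**2. What the power statement covers**

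Inputs from Power calculations: 380 attendances a week; 312 weeks, taken as 156 before and 156 after; a 2% reduction; stated power above 90%. Assumed: two-sided 0.05, because no level is stated.

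For a simple Poisson before-and-after comparison:

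SE of the log rate ratio = √[1/(156 × 380) + 1/(156 × 380 × 0.98)] = 0.00584

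|ln 0.98| / SE = 0.02020 / 0.00584 = 3.46

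Power = Φ(3.46 − 1.96) = Φ(1.50) = 0.933

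The stated figure is reproduced, but only as one test on the undivided count, with no trend term, overdispersion or autocorrelation. It says nothing about the separate age groups.

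**3. Chance of at least one false positive at 3 years**

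Three independent age groups: 1 − 0.95³ = 0.143.

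Four analyses, treated as independent: 1 − 0.95⁴ = 0.185. This is too high, because the all-age result is built from the three strata. I therefore simulated three age-group z-statistics with a common correlation, formed the all-age statistic as their weighted sum using the square root of each group's share of events, and rejected at |z| > 1.96. Equal shares and shares of 50%, 30% and 20% gave the same results to two decimals.

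| Correlation between age groups | At least one false positive, either direction | At least one false claim of benefit |
|---|---|---|
| 0 | 0.16 | 0.08 |
| 0.5 | 0.13 | 0.06 |
| 0.8 | 0.10 | 0.05 |

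For a single test the corresponding values are 0.05 and 0.025.

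**4. What naming one analysis preserves**

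With the all-age count as the single primary test, power for a 2% reduction stays at 0.933 under the model in step 2. If all four analyses stayed primary with a Bonferroni level of 0.05 / 4 = 0.0125 (critical value 2.498), all-age power would be Φ(3.46 − 2.498) = 0.83. Per-age power would be 0.17 at an assumed 20% share of events, 0.31 at one third and 0.57 at 60%. For the 5% reduction that the article expects, the same simple model gives all-age power of about 1.00 and per-age power of at least 0.92 at the 0.0125 level. The loss therefore matters at the 2% effect quoted for power, and much less at 5%.

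**The case against.** The best counter-argument is that the article already points to the all-age series. Study population takes the whole district first and stratifies afterwards, the power illustration uses the total, and Health outcomes measures puts the overall analysis before the strata. The three age bands also cover all ages, so the research question is compatible with an overall analysis that is later broken down. Both all-age and stratified results are planned, so any difference between age groups would be visible.

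Much of this stands, and it shows which analysis to name. It does not settle the matter. Study population gives an order of work, not a ranking, and Health outcomes measures places all four analyses under the primary label. Showing every result does not say which one answers the primary question.

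It is also fair to say that significance levels, multiplicity adjustments and tests of age by intervention may sit in an analysis plan that is not shown. Their absence is not part of this point. The point is that the article does define the primary outcome, and does so in ways that cannot all be followed.

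A reader might go further and infer that the 1-year and 3-year analyses are also unranked, giving eight candidate primary tests. The documents do not support that. Follow-up names 3 years as the primary period, and Table 3 and Analysis methods label 1 year as interim. The aim "to provide timely evidence for decision makers, including other local authorities on the health impacts of CAZ approaches" belongs to the sentence that justifies the 3-year period; the 1-year report appears there only in parentheses. Error rates for eight tests, or for two looks at the all-age count, therefore do not apply.

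**Conclusion.** The concern holds for the four analyses at 3 years. The primary outcome is defined inconsistently, and no statement says which analysis decides the primary question. The false-positive rate is two to about three times that of a single test, counted in either direction or as claims of benefit only.

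These rates assume a two-sided 0.05 level, no true effect in any age group, correlations of 0 to 0.8 between age-group results, and a reader free to present any of the four as primary. The power figures also assume Poisson variation without trend, overdispersion or autocorrelation, and assumed age shares. The inconsistency itself rests on none of these assumptions; it is there in the text. It should be corrected, but it does not undermine the design.

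**What to change.** In Aims and objectives, in the text of Health outcomes measures and in the primary row of Table 3, name one primary analysis: the change in the all-age weekly respiratory count at 3 years. This is the series that the power illustration uses and that Study population analyses first. Describe the analyses in children, adults and older adults as secondary. How those are adjusted or ordered can be left to the analysis plan. The 1-year analysis can keep its interim label.

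The change is one of wording and needs no new data. It should be made before post-implementation outcome data are examined. Its cost is that an isolated result in one age group could no longer be presented as the primary finding.

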#### Sampling and data collection methods

Data extraction algorithms for health outcomes will be compiled using WHO International Classification of Disease (ICD) 10 and CTV3 Read codes and applied to our cBradford and BiB data sets. Relevant CTV3 codes will be identified by mapping them to ICD-10 codes using the NHS Digital Technology Reference data Update Distribution. We will extract a range of other characteristics recorded routinely in health records including gender, age, and ethnicity to characterise outcomes along social gradients. Data will be linked to Lower Super Output area to calculate the Index of Multiple Deprivation (IMD), a measure of relative deprivation. Within the BiB cohort, in addition to linked routine data, we have detailed ongoing assessments of health, wellbeing, cognitive development and socio-economic circumstances currently underway amongst children aged 7-11, [42] along with monthly geocoded address data. This wave of data collection was completed in March 2020 (prior to implementation). This detailed baseline information will allow detailed subgroup analysis to be performed in WP3B to explore the impact of the B-CAP on health inequalities using dimensions such as SES (education, IMD, financial security and employment status) and ethnicity.

#### Analysis methods

For WP3A, demographic information from cBradford (age, sex, ethnicity, IMD and geographic location (ward level of those inside and outside the CAZ)) will be summarised using frequency (%) or mean (SD). For WP3B, information (age, sex, ethnicity, IMD, measures of SES) from the BiB cohort will similarly be summarised. An interrupted time series (ITS) design using segmented regression analysis will be used to estimate levels and trends during specific points in time (segments), where the values of the time-series may change from the previous pattern because changes in air pollution trends as a result of the B-CAP intervention. In segmented regression, terms are included in the model to indicate, for example, the baseline level of the outcome, the implementation of the intervention, and time after the intervention. These effectively fit separate regressions for “segments” so that it is possible to estimate changes in level and trend. The assumption underlying our analyses is that we would expect a slope change in our outcome measure as we expect the implementation of the B-CAP and its effects are gradual.

We will examine time-series line plots of the health outcomes to aid identification of underlying trends and seasonal patterns of the data. As the outcomes are counts, the Poisson link function will be used in the regression model. Models will be adjusted for age, sex, ethnicity, and measures of SES such as IMD. The coefficients from this regression can be used to estimate the intervention effect (the absolute difference between the predicted outcome based on the B-CAP and its counterfactual value, i.e. the expected values for level and trend if the intervention had not occurred. We will account for the disruption caused as a result of the COVID-19 pandemic, and the subsequent changes in behaviour including alterations to travel behaviour and A&E and GP attendances, through the selection of change points used in the segmented regressions. In England, the first lockdown was implemented on the 23rd of March 2020 and the third ended on the 31st July 2021. We will therefore consider four segments for our analysis: (1) the period prior to the first national lockdown from when clinical data of sufficient quality was available (October 2017 – March 2020); (2) the period spanning the lockdowns (March 2020 – August 2021); (3) the period encompassing the preparation phase for the CAZ (August 2021 - CAZ switch on, this includes other activities within the B-CAP including provision of grants for vehicle upgrades); (4) the period post ‘switch on’ of the charging CAZ). We will conduct an interim analysis at 12 months post-implementation and re-examine analyses 3 years post-implementation.

Given the seasonal variation in respiratory outcomes and pollution, data will be adjusted for seasonality. We will also assess the models for residual autocorrelation and apply ARIMA methods as necessary. We hypothesize that the B-CAP will lead to a larger decrease in outcomes for those living in more deprived areas and by ethnicity and will examine these through interaction terms and stratified analyses. We will consider a series of sensitivity analyses by varying model assumptions. We expect air pollutants to decrease the most within the CAZ boundary compared to without and will examine the impact of spatial variation on outcomes. We will test our assumption that the effects of the implementation of the CAZ are gradual, by altering the length of the third segment based on dates of when implementation activities were initiated. We will also assess lagged effects between exposures to air pollution and health outcomes.

ITS is a strong evaluation design when randomization is not possible as post-intervention trends can be compared to trends prior to the interruption of the intervention. We will strengthen this design through the inclusion of a non-equivalent control (NEC) outcome (superficial head injuries) which will not be affected by the intervention (CAZ) to control for possible concurrent events. Previous studies utilizing a NEC have used finger wounds [31]); we chose superficial head injuries given the higher number of cases per month compared to other potential injuries. A change in the outcome of interest following implementation of the CAZ with no change in the NEC would increase our confidence that the changes observed were a result of the intervention.

For WP3B, we will conduct detailed analyses on health inequalities using data from the BiB cohort, which has individual, in addition to area level, information on socioeconomic status. We will replicate analysis on respiratory outcomes looking at both combined respiratory morbidities and separately at asthma/wheeze, exploring multi-dimensional measures of socio-economic status, [68] ethnicity, deprivation, employment, religion, education and social capital using the PROGRESS framework as a guide to selecting relevant indicators [57].

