#### Power calculations

In order to explore power of the ITS analysis to detect changes in health outcomes we have consulted a range of epidemiological studies and systematic reviews, along with identification of relevant intervention studies for effect sizes. Our own research has found that a 10μg/m3 increase in NO_2_ is associated with a 9% increase in the odds of low birthweight, while a 5μg/m3 increase in PM2.5 is associated with an 18% increase in odds of low birth weight [58]. For other health outcomes, systematic reviews have shown a 10μg/m3 increase in NO_2_ to be associated with increases in respiratory disease hospital admissions ranging between 0.57-3.5%, and a 0.66% increase in admissions for cardiovascular admissions, with stronger effects among children and the elderly [59–63].

Recent intervention studies (reviewed earlier) offer no consistent results. Based on the evidence reviewed and working on the assumption the B-CAP will reduce NO_2_ by between 12-18μg/m3 we have estimated a 5% reduction in health outcomes (emergency / GP attendances and incidence related to both respiratory and cardiovascular outcomes); and a 2% reduction in adverse birth outcomes. A 5% reduction in emergency attendances in relation to respiratory and / or cardiovascular illness would likely have substantial cost-savings for the NHS [64].

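### The primary time series analysis assumes a gradual slope change, the follow-up section expects an immediate fall, and the stated power is tied to neither effect

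*Protocol article*

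**What the plan says.** Four places in the protocol article bear on the effect of interest for the primary outcome, weekly respiratory attendances.

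- **Work package 3, Analysis methods, on shape.** The working assumption is stated as follows: "we would expect a slope change in our outcome measure as we expect the implementation of the B-CAP and its effects are gradual". The same paragraph says of the model terms: "These effectively fit separate regressions for “segments” so that it is possible to estimate changes in level and trend". Neither term is named as the primary one.
- **Work package 3, Analysis methods, on the effect.** The intervention effect is "the absolute difference between the predicted outcome based on the B-CAP and its counterfactual value, i.e. the expected values for level and trend" had the intervention not occurred. No week, year or averaging window is given. The model has four segments: before lockdown, lockdown, preparation, and after switch-on.
- **Follow-up.** "we would expect to see an immediate reduction in emergency and GP attendances related to respiratory (adults and children) and cardiovascular (adults only) events". The same section expects legal compliance at 1 year with gradual improvement after that, and sets 3 years as the primary follow-up with interim reporting at 1 year.
- **Power calculations.** The effect expected is given as "we have estimated a 5% reduction in health outcomes". For the primary outcome, "we observed an average of 380 respiratory attendances per week" in a pilot subsample of 316,585 people, 312 weekly points are planned, and guidance from cited simulations "suggests we will have > 90% power to detect a 2% reduction in admissions". Neither percentage is said to be a step, a mean over follow-up or a value reached at 3 years.

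**The concern.** In a segmented regression an immediate reduction is the level term and a gradual one is the trend term. They are different parameters with very different precision. The article expects one in its analysis section and the other in its follow-up section, for the same outcome.

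Three things follow. The power claim cannot be assessed until the effect is named. A flat result at the 1-year report would contradict one section and fit the other. If level and slope are both estimated and neither is primary, the more favourable can be put forward afterwards.

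**Working it through.** **Inputs from the article:** 380 attendances a week; 312 weekly points, taken as 156 before and 156 after; a 2% detectable and a 5% expected reduction; four segments with change points at March 2020, August 2021 and switch-on in 2022.

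**Assumptions:** two-sided 5% (the article states no level); pure Poisson with a flat baseline rate and no autocorrelation; two seasonal harmonics where seasonality is included; segments of 128, 71, n3 and 156 weeks. The preparation length n3 is varied because switch-on is given only as 2022.

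**Formula:** power = Φ(|effect| / SE − 1.96), counting only findings in the direction of benefit. The SE comes from the inverse Poisson information matrix. Effects are on the log scale: ln 0.98 = −0.0202 and ln 0.95 = −0.0513. A slope reaching the reduction at 3 years is that value divided by 3, per year.

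**Step 1: the plan's own figure.** For a step with no trend term, SE = √(2 / (156 × 380)) = 0.00581. Then 0.0202 / 0.00581 = 3.48, and Φ(3.48 − 1.96) = 93.6%. The claim of above 90% is reproduced.

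**Step 2: other readings of the same 2%.** The last column scales counts to 380 × 530,000 / 316,585 ≈ 636 a week, which assumes the same rate in the full population.

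| Effect | SE at 380 | Power at 380 | Power at 636 |
|---|---|---|---|
| Step, no trend | 0.58% | 94% | 99% |
| Step, with baseline trend and seasonality | 1.20% | 39% | 59% |
| Slope change reaching 2% at 3 years | 0.67% per year | 17% | 25% |
| Four segments, level, n3 = 30 to 74 | 2.21% to 1.48% | 15-28% | 22-42% |
| Four segments, slope reaching 2% at 3 years, n3 = 30 to 74 | 5.96% to 1.53% per year | 3-6% | 4-8% |

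A slope change averaging 2% over the 3 years, in the pre/post model, has 52% power at 380 a week.

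**Step 3: extra variation.** With overdispersion 2 and lag-1 autocorrelation 0.3 (illustrative values), the first three rows at 380 a week fall to 44%, 14% and about 8%.

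**Step 4: the 5% effect in the four-segment model, 380 a week.** For n3 = 40, 60 and 74 weeks, power for an immediate level change is 75%, 89% and 93%. For a slope reaching 5% at 3 years it is about 6%, 13% and 20%.

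**Step 5: a 3-year mean difference from the counterfactual.** This combines level and slope, and it extrapolates the preparation-segment trend for 3 years. Its SE is 7.4%, 4.3% and 3.3% for n3 = 40, 60 and 74. Power for an immediate, sustained 5% effect is 10%, 22% and 34%.

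**Step 6: testing level and slope separately at 5% each.** The two estimates correlate at 0.75, 0.63 and 0.52 for the same n3. The chance of at least one false positive is then 8.1%, 8.7% and 9.0%.

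**The case against.** The two sections can be partly reconciled. In Follow-up, the word immediate derives from the short lag between pollution and attendances, and it contrasts attendances with birth outcomes. If pollution falls gradually and health responds without delay, attendances also fall gradually. The analysis section calls gradual effects an assumption, tests it by varying the preparation segment, and assesses lags. This softens the contradiction but does not remove it: the text still predicts an immediate reduction, and changing a segment's length does not choose between level and slope.

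A reader might infer that no effect is defined at all. That goes too far. The counterfactual difference uses both terms and 3 years is the primary follow-up. What is missing is the time point or window, and a full analysis plan may supply it. The conflicting expectations and the unlabelled 2% are nevertheless in this article.

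A reader might also infer that the power figure is wrong. The cited simulations are not at hand and may define the effect, so the criticism is that the article does not say which effect is meant, and that only one simple reading reproduces the figure.

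Two larger magnitudes are tempting and not supported. A many-fold gap between the shapes at 1 year needs a ramp lasting the full 3 years, whereas the article expects compliance at 1 year; a linear ramp reaching 5% by then would average 2.5% in that year, a two-fold gap. A false-positive risk of 1 − 0.95² = 9.75% needs independent estimates, and these are correlated. The 1-year report also carries no stated decision rule.

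**Conclusion.** The point holds in this form: the article gives two expected shapes for the primary outcome, sets no time point for its counterfactual difference, and does not tie its power to any one effect. The stated power is reproduced only for a step with no trend term, which is not the model described. For a 2% effect at 380 a week it drops to 39% or 17% in a pre/post model with trend and seasonality (step or slope). In the four-segment model it is about 15-28% or 3-6%. If counts scale to about 636 a week, these become 59%, 25%, 22-42% and 4-8%. Testing level and slope separately carries about 8-9% false-positive risk.

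The figures rest on an assumed two-sided 5% level, Poisson variation only, a flat baseline and assumed segment lengths. The pupil monitoring schedule implies switch-on between Spring and Summer 2022, so the longest preparation segments, which give the highest power, are the least likely. The findings do not show that an immediate 5% effect would be missed: the level term has 75-93% power for it at n3 = 40-74 weeks before overdispersion and autocorrelation.

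**What to change.** 1. State one expected impact shape, in the same words, in the Work package 3 analysis section and in Follow-up. If a mixed shape is meant (some immediate fall, then further decline), say so in both.
2. Before analysis, name the primary contrast and the time point or window for the counterfactual difference, with the remaining level and trend terms as secondary.
3. Restate the power for that contrast under the planned four-segment model, with seasonality, overdispersion and autocorrelation, and say whether the 2% and 5% are steps, means or values at 3 years.

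Compute the precision of candidate contrasts before choosing. The 3-year mean difference is a natural candidate, but it has only about 10-34% power for a 5% effect at 380 a week, because it extrapolates a short preparation segment. It should not be adopted by default.

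The cost is wording in three sections and one recalculation, with no new data. The restated power will probably be well below 90% for a 2% effect.
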